## Abstract

**Background:**

Breastfeeding protects against a range of conditions in the infant, including sudden infant death syndrome (SIDS), diarrhoea, respiratory infections and middle ear infections [1, 2]. The World Health Organization (WHO) recommends exclusive breastfeeding until six months of age, with continued breastfeeding recommended for at least two years and other complementary nutritious foods [3]. The 2017-18 National Health Survey (NHS) and 2018-19 National Aboriginal and Torres Strait Islander Health Survey (NATSIHS) reported that the proportion of breastfeeding in Aboriginal and Torres Strait Islander infants (0–2 years) were less than half that of non-Indigenous infants (21.2% vs. 45%, respectively)[4]. There is a lack of research on interventions supporting Aboriginal women to breastfeed, identifying an evaluation gap related to peer support interventions to encourage exclusive breastfeeding in Aboriginal women.

**Methods:**

We will evaluate the effect of scheduled breastfeeding peer support for and by Aboriginal women, on breastfeeding initiation and the prevalence of exclusive breastfeeding. This MRFF (Medical Research Future Fund) funded project is designed as a single-blinded cluster randomised controlled trial recruiting six sites across New South Wales, Australia, with three sites being randomised to employ a peer support worker or undertaking standard care. Forty pregnant women will be recruited each year from each of the six sites and will be surveyed during pregnancy, at six weeks, four and six months postnatally with a single text message at 12 months to ascertain breastfeeding rates. In-depth interviews via an Indigenous style of conversation and storytelling called ‘Yarning’ will be completed at pre- and post-intervention with five randomly recruited community members and five health professionals at each site” [5]. Yarns will be audio recorded, transcribed, coded and thematic analysis undertaken. Health economic analysis will be completed to assess the health system incremental cost and effects of the breastfeeding intervention relative to usual care.

**Discussion:**

Evidence will be given on the effectiveness of Aboriginal peer support workers to promote the initiation and continuation of breastfeeding of Aboriginal babies. The findings of this study will provide evidence of effectiveness and cost-effectiveness of including peer support workers in postnatal care to promote breastfeeding practices.

**Trial Registration:**

ACTRN12622001208796 The impact of breastfeeding peer support on nutrition of Aboriginal infants

**Supplementary Information:**

The online version contains supplementary material available at 10.1186/s12889-023-15558-2.

## Background

Breastfeeding protects against a range of conditions in the infant, including sudden infant death syndrome (SIDS), diarrhoea, respiratory infections and middle ear infections [1, 2]. There are also later benefits associated with being breastfed, for both children and adults, such as a lower risk of developing obesity in childhood, diabetes in adulthood and other later cardiometabolic disorders [2, 6]. Breastfeeding also benefits women, including more rapid weight loss after birth, and reduced risk of breast and ovarian cancer in the premenopausal phase of life [2, 7].The World Health Organization (WHO) recommends exclusive breastfeeding until six months of age, with continued breastfeeding recommended for at least two years and providing of other complementary nutritious foods [3]. Similarly, Australian National Health and Medical Research Council (NHMRC) guidelines recommend that infants are exclusively breastfed until around six months of age, at which age solid foods are introduced, and recommends that breastfeeding is continued until 12 months of age and beyond [2].

Data collected from the 2017-18 National Health Survey (NHS) and 2018-19 National Aboriginal and Torres Strait Islander Health Survey (NATSIHS) in Australia reported that the proportion of Aboriginal and Torres Strait Islander infants (0–2 years) currently being breastfed was half that of non-Indigenous infants (21.2% vs. 45%, respectively)[4]. Data also showed that Aboriginal And Torres Strait Islander infants had higher rates of never being breastfed (13.0% vs. 7.7%, respectively)[4].

The 2012-3 Australian Aboriginal and Torres Strait Islander Health Survey reported that Aboriginal infants aged 0–3 months in New South Wales (NSW), Australia were exposed to the lowest rates of breastfeeding (12%) compared to other Aboriginal or non-Aboriginal infants in other states [8].

Aboriginal and Torres Strait Islander infants are also more likely to be weaned onto solid foods before six months of age; 45% of infants received soft/ solid food by four months, compared with 28% of non-Indigenous infants [9]. Early weaning increases the risk of gastroenteritis, [2] particularly in environments where hygiene practices required for sterilising bottles may not be easily achieved or maintained, as in the case of overcrowding.

In addition to health implications, commercial infant formula creates an additional economic burden to families, compared to breastfeeding [9, 10]. The total value of breastfeeding to the community makes it one of the most cost-effective primary prevention measures available [2, 11, 12]. A number of studies have calculated the potential economic benefits of breastfeeding. A United States analysis showed that if 90% of families could exclusively breastfeed for six months, the country would save $13 billion per year in healthcare costs and prevent an excess 911 deaths per year, nearly all of whom would be infants [13]. An Australian study has estimated that the hospital-related cost of premature weaning for four conditions (gastrointestinal illness, respiratory illness, eczema and necrotising enterocolitis) as AU$60–120 million per annum [14]. In Canada, McIsaac [15] calculated the proportion of three infectious outcomes and one mortality outcome that could be prevented in infancy by breastfeeding for First Nations Métis and Inuit populations. Between 5.1% and 10.6% of otitis media, 24.3 − 41.4% of gastrointestinal infection, 13.8 − 26.1% of hospitalisations from lower respiratory tract infections, and 12.9 − 24.6% of sudden infant deaths could be prevented in Aboriginal and Torres Strait Islander infants if they received any breastfeeding. No such calculations have been carried out for Aboriginal or Torres Strait Islander Australians.

### Interventions

There is good evidence for including peer support interventions to support women’s decision to initiate breastfeeding and continue for a longer period of time [16, 17]. A Cochrane review of interventions to increase breastfeeding in infants born at term; had more than 83,246 mother-infant pairs from 73 studies that contributed data (58 individually-randomised trials and 15 cluster-randomised trials) [18]. Overall, interventions increased exclusive breastfeeding rates and duration. Several factors that contributed to the successful interventions that encouraged exclusive breastfeeding included: advice offered as part of routine care by trained personnel during antenatal or postnatal care; ongoing scheduled visits; and advice that was tailored to the setting and needs of the specific population group. Other characteristics of successful strategies included interventions delivered with a face-to-face component, lay/ peer support, and a specific schedule of four to eight contacts [18]. The evidence [18] identified that mixed mode interventions, combinations of face-to face and other media support, were effective when they start from pregnancy and continues to postnatal period [17]. Support was more likely to be effective in settings that had already high breastfeeding initiation rates. One of the studies included in the Cochrane review, a cluster randomised controlled trial of motivational interviewing to extend the duration of lactation in 300 women in regional NSW [19], showed a greater prevalence of exclusive breastfeeding in the intervention group at four months (adjusted OR 1.88; 95%CI 1.01–3.50; p = 0.047). A rapid evidence review to inform the Australian Breastfeeding Strategy notes that evidence from the most recent comprehensive systematic reviews highlights that additional education or support for mothers of any kind within the healthcare system, compared with usual care, increases the likelihood of breastfeeding by 10–30%. Interventions that included peer counselling were more effective than those without peer counselling [10]. Studies also confirmed that face-to-face care is more effective than other communication, for example printed materials. Nevertheless, interventions involving technology as an adjunct to other postnatal support have recently been found to increase exclusive breastfeeding [10, 20].

There is almost no research on interventions to support Aboriginal and Torres Strait Islander women to breastfeed, identifying an evaluation gap related to peer support interventions to encourage exclusive breastfeeding in Aboriginal and Torres Strait Islander women. There is a need for translational research and for capacity-building based on the effectiveness and cost-effectiveness of community-based social mobilisation and breastfeeding education activities. Our study addresses that evidence gap.

Successful breastfeeding interventions conducted in Aboriginal and Torres Strait Islander populations in other countries include: peer counselling support, multifaceted components that are culturally appropriate; inclusion of social marketing techniques; provision of more baby-friendly healthcare services; inclusion of individual education and support; and targeting of family members including the grandmother [10]. In Australian, a review of current evidence points towards models of care that provide continuity of care, delivered by Aboriginal and Torres Strait Islander community-controlled organisations, Aboriginal and Torres Strait Islander health professionals and employed peer workers as most effective [10].

There is minimal published research internationally for the cost of peer support, or even professional support, for lactation support. In one trial, similar to our proposal, the FEeding Support Team (FEST), conducted a randomised, controlled feasibility trial of proactive and reactive telephone support for breastfeeding women living in disadvantaged areas in Scotland, with follow-up at six weeks. The incremental cost of providing proactive calls was £87 per additional woman breastfeeding and £91 per additional woman exclusively breastfeeding at 6–8 weeks [21].

The Australian Breastfeeding Association (ABA) is Australia’s most prominent non-government organisation supporting breastfeeding families. They developed and first delivered a training program for community breastfeeding mentors in Aboriginal communities in in NSW in 2019 and included Aboriginal workers in maternal and child health programs and community members. We plan to use this training model to train workers. We are not aware of paid positions for Aboriginal peer workers that continue beyond the six-week postnatal period. Our review of online resources to support Aboriginal women to breastfeed revealed few resources that are culturally appropriate to support Aboriginal families to breastfeed[22] but included some websites, pamphlets and video resources[22] [23].

### Pilot work

In 2016, we initiated a lactation support group in response to low breastfeeding rates in one location in regional NSW, Australia. The support group, held at a local cultural centre, was run by a child health nurse and an Aboriginal Health Worker and included an Aboriginal peer support volunteer. Following zero attendance at this lactation support group, we undertook a small qualitative research project (unpublished) to interview Aboriginal women with infants about the facilitators and barriers to breastfeeding. Women reported negative and positive feedback about their experiences related to breastfeeding advice that had been provided by health professionals. Some women found it difficult to access advice when they were experiencing difficulties with breastfeeding, including after-hours access for support. Women did not state that they were concerned about breastfeeding in public or about the effects of breastfeeding on their appearance. One participant noted that access to a face-to-face online resource was useful. However, most participants were unaware of this service, or reported that they could not afford to access a lactation consultant.

### Objectives

This project aims to improve the nutrition of Aboriginal and Torres Strait Islander infants.

Our objective is to evaluate the effect of scheduled breastfeeding peer support for and by Aboriginal women, on breastfeeding initiation and the prevalence of exclusive breastfeeding at six weeks, four months and six months post–birth. The intervention will utilise face-to-face peer support provided for and by Aboriginal women and employ innovative aspects such as social media, video and telephone calls by Aboriginal peer workers for six months postnatally.

## Methods/design

### Overview

The project design is a single-blinded cluster randomised controlled trial of an Aboriginal peer support worker to support the initiation and maintenance of breastfeeding over the first six months of life. Other research objectives include the evaluation of the role of these workers via qualitative interviews/yarns with community and health professionals, and development and evaluation of video resources for community members. The schedule of enrolment, intervention and data collection can be found in Fig. 1.

**Fig. 1 Fig1:**
[figure not shown]
Marri Gudjaga — SPIRIT schedule of enrolment, intervention and data collection

### RCT

#### Sites/Setting

The RCT will include six Aboriginal maternal and child health services in NSW (NSW Aboriginal Maternal and Infant Health Services, and Aboriginal Community Controlled Health Services).

NSW was chosen as the geographical area to sample because Aboriginal women in NSW have the lowest initiation rates for breastfeeding and the highest decline in exclusive breastfeeding rates in the country [9]. In NSW, much of the antenatal care for Aboriginal women is delivered through Aboriginal Community Controlled Health Organisations (ACCHOs) and through Aboriginal Maternal and Infant Health Service (AMIHS) via NSW Health. Some Aboriginal women access mainstream general practices, hospital antenatal clinics and private obstetricians. For the purpose of this study, we anticipate recruiting women attending antenatal care services that target Aboriginal communities specifically, including the maternal and child health services within the AMIHs network, which includes 40 services, as well as an independent community-controlled maternal and child health service. These services provide care to Aboriginal women, both antenatally and postnatally.

Peer workers will be recruited at intervention sites, including via Aboriginal community networks. The workers will be employed by the University of Wollongong (UOW) but work within the partner organisations under a Memorandum of Understanding (prepared by the UOW legal team in conjunction with individual Local Health Districts or organisations), under the supervision of the UOW team.

Participating sites will be offered compensation for involvement in the trial including funds for infrastructure support for the peer worker (including funding for fuel/ transport costs, and office infrastructure such as computer and phone). Sites are also offered funding to support workers including the peer worker and 1–2 other health care workers to attend annual training workshops/ seminars.

#### Sample size

We plan to recruit a total of 720 participants (120 at each site), allowing for a predicted 15% drop out at 6 months post-birth, resulting in 612 participants for analyses.

A similar intervention, the RUBY Study (Forster et al., 2017) was able to follow-up 88% of participants so we believe a 15% drop-out rate is likely conservative.

#### Participant inclusion criteria

Aboriginal or Torres Strait Islander women or non-Aboriginal women who have an Aboriginal or Torres Strait Islander infant that they are breastfeeding will be included. Participants (mothers) will be over 14 years of age. Those who are aged 14–17 will need to obtain parental/guardian permission for involvement.

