#### Participant recruitment

Recruitment of participants will be conducted from 28 weeks gestation and survey collection will occur from 32 weeks gestation with care to recruit young and marginalised women to prevent under-sampling.

Staff at the participating sites will offer the woman a show bag containing information about the project, giveaways (as determined by staff at the site, funded by the project), and the Participant Information Statement PIS). Staff will ask verbal permission from the participant to pass on their mobile phone number (landline and/or email) to the research team so they may to be contacted regarding the study.

Staff at the sites will record the potential participant’s name on a log that contains the woman’s name, mobile number, and Estimated Due Date (EDD). This information will be scanned by the staff member and emailed or faxed to the research team, weekly.

All participants will be provided with a $50 gift card at the six-week interview (6 weeks post-birth) as an incentive for participating in the project. Those who do not have a mobile phone can be provided with one as part of the project.

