#### Data collection

A research assistant or associate research fellow will collect data. The research team will call potential participants that have provided their contact details. They will again be verbally given information about the project, from the PIS and will be asked to provide verbal consent. Surveys will be collected at these time-points (see Fig. 2):

Baseline (32–40 weeks of gestation).6 weeks post-birth (after which a $50 voucher will be sent to participant).4 months post-birth.6 months post-birth.12 months post-birth (SMS message).

If participants are not contactable by telephone after three attempts, a link to the survey will be emailed to them or sent via SMS (to a maximum of three times over three weeks). Permission will also be requested for the maternal and child health team to inform peer workers when the women have given birth to their babies, in order to ensure early access to the intervention.

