#### Intervention

##### Peer support workers will be employed three days a week for three years in three communities

We plan an **evidence-based, culturally appropriate and best practice intervention** designed with the aim to improve the initiation of breastfeeding and support the continuation of exclusive breastfeeding to best practice standards. Following the systematic review of the evidence the intervention will include:

Employment of Aboriginal breastfeeding peer support workers, who community mentor training, provided through the ABA. Trained Aboriginal peer support workers will then be hosted by maternal and child services in three sites randomised to receive the intervention.

The intervention group will receive scheduled breastfeeding Aboriginal peer breastfeeding support at an antenatal visit, then again within the first week after birth and then support over the following 6 months. The peer workers will provide support such as weekly telephone calls and/or SMS text messages for 6 weeks after birth, along with face-to-face visits where possible (for example clinic visits, mothers’ group or home visits when accompanying other staff). As appropriate, video-chats will be included, as part of a program of monthly Aboriginal peer worker video-chats (via smart-phone video) about breastfeeding. Opportunistic support will also be provided for emerging issues, for example nipple pain. If required, breastfeeding technical support will be sought by the Aboriginal peer support workers from experienced midwives, Aboriginal Health Workers (AHWs), Aboriginal Health Practitioners, ABA counsellors or lactation consultants, or women would be referred to these health care professionals for medical support (such as support for mastitis). Our team will offer cultural safety training for ABA peer counsellors and lactation consultants where appropriate, to ensure they can provide local, culturally appropriate/informed technical support for the Aboriginal peer workers and women.

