At 6 weeks we expect a prevalence of exclusive breastfeeding to be 25% in the control group, based on breastfeeding prevalence of 26% seen at 6 weeks in the Gudaga study (Craig et al., 2011) while if effective we estimate prevalence of exclusive breastfeeding in the intervention group to be 40% or more. A Cochrane review by McFadden et al. [18] reported women in intervention groups were less likely to stop exclusive breastfeeding by 6 weeks (RR 0.79, 95% CI 0.71 to 0.89)., which applied to a base rate of 75% stopping breastfeeding leads to 15% higher absolute breastfeeding rates at 6 weeks (40% vs. 25%). However, we consider the current study intervention to be more intense than other studies included in that meta-analysis.

Elliot-Rudder [19] conducted a cluster RCT where health professionals were trained in motivational interviewing to support women to continue breastfeeding. In a sample of 330 women, with the outcome of exclusive breastfeeding at 4 months (OR 1.88, 95% CI 1.01–3.6, p = 0.047), this study was able to demonstrate effectiveness of the intervention.

We plan to use survival analysis to assess one of our secondary outcomes (using another outcome, days of exclusive breastfeeding).

We will recruit approximately 120 mother – babies in each of six sites (aiming for 40 per year for 3 years, given approximately 80–100 births per year in each site).

Primary outcomes: (a) Exclusive breastfeeding at 6 weeks (24 h recall telephone questionnaire or via survey email). (b) Exclusive breastfeeding at 4 months (24 h recall telephone or survey email) (c) Exclusive breastfeeding at 6 months (24 h recall telephone or survey email).

Secondary outcomes: (a) Initiation of breastfeeding within first 24 h (self – report, 6 week survey), (b) Days of exclusive breastfeeding (self-report) (c) Days of any breastfeeding (self-report) (d) Age at introduction of expressed breastmilk (self-report). (e) Age introduction of solid/semi-solid food (self-report) (f) Age at introduction of other breastmilk substitutes (self-report) (g) Reason for cessation of breastfeeding including contraindications to breastfeeding (self-report) (h) Hospitalisation in first 6 months of life (self – report at six months) (i) Otitis media requiring antibiotics in first six months of life (self – report at six months). (j) Breastfeeding at 12 months (SMS – yes/ no).

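### Eligibility is worded in terms of an infant currently being breastfed, but women are enrolled in pregnancy and starting to breastfeed is an outcome

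*Protocol article*

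**What the plan says.** Under Participant inclusion criteria, the Protocol article names Aboriginal or Torres Strait Islander women and then adds that "non-Aboriginal women who have an Aboriginal or Torres Strait Islander infant that they are breastfeeding will be included". The only other conditions there concern age and parental permission. No other section restates or interprets the breastfeeding clause.

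The sections that describe how the trial runs place entry before birth:

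- Abstract, Methods: "Forty pregnant women will be recruited each year from each of the six sites".
- Participant recruitment: "Recruitment of participants will be conducted from 28 weeks gestation and survey collection will occur from 32 weeks gestation".
- Data collection: the baseline survey falls at 32 to 40 weeks of gestation.
- Intervention: the intervention group receives "scheduled breastfeeding Aboriginal peer breastfeeding support at an antenatal visit", with further contacts after birth.

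Starting to breastfeed is something the trial sets out to measure. The Objectives section aims to evaluate the effect "on breastfeeding initiation and the prevalence of exclusive breastfeeding at six weeks" and at later times. Under Analysis, secondary outcome (a) is "Initiation of breastfeeding within first 24 h".

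**The concern.** An eligibility rule has to be answerable when a woman is enrolled. This one refers to an infant already born and being breastfed, while every woman enters during pregnancy. Site staff therefore either ignore the rule or apply it later.

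Applying it later is the harmful case. Sites are already allocated and the first peer contact is scheduled before birth, so whether a woman breastfeeds may itself be a result of the intervention. Removing women who do not breastfeed would then remove different kinds of women from the two arms. A woman who starts only because of the peer worker would stay in at an intervention site, and a similar woman at a control site would drop out. Randomising sites does not protect against selection made after allocation. The initiation outcome would be compared in a group chosen largely on initiation, and exclusive breastfeeding would be compared between groups that may no longer be alike.

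**Working it through.** **1. The passages side by side.** Recruitment starts at 28 weeks, baseline is at 32 to 40 weeks, and the first intervention contact is antenatal. The condition can first be true after birth. The order is therefore site allocation, enrolment, antenatal contact, birth, and only then a status that could satisfy the criterion. It is a post-randomisation event.

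**2. Two readings of the sentence.**
- Broad: the clause covers all women. Every participant is then subject to a condition that cannot be assessed at entry.
- Narrow: the clause covers only non-Aboriginal mothers. Aboriginal and Torres Strait Islander women then enter without a feeding condition, and non-Aboriginal mothers enter under one that cannot be assessed. The article gives no share of non-Aboriginal mothers, so the number affected cannot be computed.

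**3. The plan's own power figure.** Inputs from Analysis: 3 sites per arm, 102 completers per site, 25% against 40%, intra-cluster correlation 0.01, two-sided pooled Z-test at 0.05.
- Design effect: 1 + (102 − 1) × 0.01 = 2.01.
- Effective number per arm: 306 / 2.01 = 152.2.
- Standard error under the null: √(2 × 0.325 × 0.675 / 152.2) = 0.0537. Under the alternative: √((0.40 × 0.60 + 0.25 × 0.75) / 152.2) = 0.0530.
- Power: Φ((0.15 − 1.96 × 0.0537) / 0.0530) = Φ(0.845) = 80.1%, as stated.
- Drop-out: 720 × 0.85 = 612, as stated.

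Nothing in this calculation depends on the eligibility clause.

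**4. Illustration on the broad reading only.** The Background gives 13.0% of Aboriginal and Torres Strait Islander infants as never breastfed, from national surveys of infants aged 0 to 2 years. Using it here is an assumption.
- Control women affected: 0.13 × 360 = 46.8, about 47. At assumed shares of 20% and 30%: 72 and 108.
- Exclusive breastfeeding among those who ever breastfed is the planned rate divided by the initiation rate, if 25% and 40% are rates among all mothers. Power below holds 306 completers per arm.

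| Initiation, control / intervention (assumed) | Control | Intervention | Difference | Power |
|---|---|---|---|---|
| No selection | 25.0% | 40.0% | 15.0 points | 80.1% |
| 87% / 87% | 28.7% | 46.0% | 17.2 points | 87.9% |
| 80% / 90% | 31.3% | 44.4% | 13.2 points | 66% |
| 70% / 85% | 35.7% | 47.1% | 11.3 points | 52% |

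The contrast widens if initiation is equal in the arms and narrows in the two scenarios where peer support raises it. Neither the direction nor the size can be read from the documents.

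**The case against.** The strongest reply is that this is loose wording and not a plan to exclude anyone. No section describes an eligibility check after birth or the removal of women who never start. The operating sections enrol pregnant women without any feeding condition. The only loss between 720 and 612 is 15% drop-out. Initiation is listed as an outcome, which makes little sense if non-initiators were to be removed. The clause can also naturally be read as describing only which non-Aboriginal mothers qualify.

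All of that stands, and it limits the claim. It does not remove the contradiction, because the eligibility statement is the rule that six sites and later readers would apply, and neither reading can be applied at 28 to 40 weeks.

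A reader might infer three stronger things that the documents do not support:

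- *Initiation would be 100% in both arms and its effect could not be estimated.* Outcome (a) is initiation within 24 hours, and a woman who is breastfeeding may have started later. On the narrow reading, Aboriginal and Torres Strait Islander mothers are not selected at all.
- *About 47 control women will be lost and the control rate will be 28.7%.* These figures need the broad reading, application after birth, and a national figure carried over to these sites. They also use never breastfed, while the clause speaks of current breastfeeding; a check some weeks after birth would exclude a different and larger group.
- *The trial was meant to include women whatever their feeding intention.* The article does not say so. An intention to breastfeed may have been meant, and nothing settles it.

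**Conclusion.** The criterion is wrong as written. It cannot be assessed at enrolment, and it conflicts with Participant recruitment, Data collection, Intervention, Objectives and the outcome list. This holds on either reading of the sentence and rests on no calculation.

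The harm is conditional. If the clause is ignored, only the wording is at fault. If it is applied after birth, it selects all women, or non-Aboriginal mothers only, on an event the intervention targets. That would distort the initiation comparison and could bias the exclusive breastfeeding comparison in either direction. The size is unknown; about 47 of 360 control women is an illustration under the assumptions given, not an expected loss. The documents do not show that any such exclusion is planned.

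**What to change.** Reword the criterion so that it uses only facts known at recruitment: pregnant at 28 or more weeks, attending a participating service, and expecting an Aboriginal or Torres Strait Islander infant. Delete the clause on current breastfeeding. Add one sentence stating that no enrolled woman is excluded from the analysis because of her feeding status after birth. If the investigators did intend a condition on feeding intention, they should say so explicitly and say how it is established before birth.

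The cost is a short amendment to the eligibility text. Sample size, drop-out allowance and the stated 80.1% power are unchanged. It should be made before any woman is screened out or removed under the present wording; if any already has been, the number in each arm should be reported.
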